### Statistical Analysis

The analysis will be done using a set of steps. The baseline characteristics of the participants will be compared between the intervention and control groups, using independent 2-tailed *t* test for continuous variables and Chi-square test for categorical variables. Delta analysis (D%) will be used to assess the change in the vaccination rate between preintervention (t0) and postintervention (t1), contrasting this change within the intervention and control groups. This will be complemented by an effect size assessment to quantify the difference in change between the 2 groups (Cohen *d* test will be used). Hierarchical level modeling will be conducted to consider any cluster effect of the clinics (defaulters will be treated as intent-to-treat analysis in the primary outcome of the study). For the secondary outcome, survival analysis will be used to further contrast the difference in the secondary outcome (proportion of defaulters) between the intervention and comparison groups, postintervention (t1). Stata will be used for the data analysis.

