### Study Design

This will be a cluster randomized controlled trial to evaluate the effectiveness of using an app to record the vaccination schedule, including reminders for parents, on increasing immunization coverage of Syrian children at the Zaatari refugee camp in Jordan. In March 2019, the study was announced through posters in Arabic, in the clinics. Clinicians and social workers will also inform the residents of the camps about the study. Parents interested in joining the study will be fully briefed about the study, and an informed consent form will be signed. After completing the consent form, participants (1) included in the app intervention arm (ie, children immunization app [CImA] recipients) will receive the usual care, access to the CImA app, and instructions on how to use it, in addition to updating their children vaccination card, or (2) under the usual care (control arm) of the trial, where they will receive the usual information on the benefits of vaccination, the child’s yellow vaccination card will be updated, in addition to the list of appointments for the future vaccines. The vaccination sites will be enrolled on the basis of convenience, because of the security situation in the refugee camp.

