### Intervention

The parents will be recruited to the study by trained volunteers at the 7 local clinics, providing vaccinations, around the Zaatari camp (Figure 1). Inclusion criteria will be the following: having at least one child of 0 to 5 years, being a local resident of the camp, and having an Android smartphone that can allow CImA app installation.

The intervention includes an app that will (1) allow storing Jordanian vaccination records (Table 1), per child, on the parents’ smartphones, in Arabic and English (in an interchangeable fashion), (2) have a set of automated reminders before the appointment of each child, and (3) in addition, summarize immunization records in the form of *due*, *taken*, or *overdue* appointments, labeled in orange, green, and red, respectively.

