### Assessments

Baseline will include the collection of our primary and secondary outcomes that are needed for the pre and postdata measurements. This includes social demographic data, any previous vaccination history, and electronic health literacy [27]. Participants, in both study arms, will be monitored for their follow-up visits to the clinic for the vaccination doses. The vaccination cards of both study arms will be marked as *intervention* or *control* arm; thus, the clinic nurses will notify the field workers about the follow-up visits. For the study outcome measures, we will measure any differences in the proportion coming back on time for the follow-up vaccination visit. The secondary outcome is the utility of the CImA app.

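### Baseline comparisons between arms use t and Chi-square tests that ignore clinic clustering, so their p-values would mislead about allocation quality; a descriptive table should replace them

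*Protocol article*

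**What the plan says.** Study Design in the protocol article states: "This will be a cluster randomized controlled trial to evaluate the effectiveness of using an app to record the vaccination schedule". The Intervention section has parents recruited "at the 7 local clinics, providing vaccinations, around the Zaatari camp".

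The first step in Statistical Analysis is the baseline comparison: "The baseline characteristics of the participants will be compared between the intervention and control groups, using independent 2-tailed". The sentence goes on to name the t test for continuous measures and the Chi-square test for categorical ones. No allowance for clinic is mentioned at this step.

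The same paragraph then contrasts the change in vaccination rate from before to after the intervention between the arms, with an "effect size assessment to quantify the difference in change between the 2 groups" based on Cohen d. Clustering appears only after that: "Hierarchical level modeling will be conducted to consider any cluster effect of the clinics".

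On what is collected at baseline, Assessments lists the outcomes needed for the before and after measurements, and adds: "This includes social demographic data, any previous vaccination history, and electronic health literacy". Child age is not named separately.

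**The concern.** The plan accepts that participants from the same clinic may be alike when it models the outcome, but not when it compares the arms at baseline. If whole clinics go to one arm or the other, a baseline difference between arms is a difference between two small groups of clinics. A test that counts each participant as an independent observation understates the chance variation in that difference, and its p-value is too small whenever the ICC is above zero.

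What is at stake is how the baseline table is read. Study Design says the sites are enrolled by convenience because of the security situation, so readers will look closely at whether the arms are comparable. Several small p-values could be taken as evidence of a faulty allocation when they are what chance between about 7 clinics produces. The differences in the sample would be real; only the p-values attached to them would be wrong.

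**Working it through.** **The plan's own figures.** Sample Size Calculation gives 374 children, raised to 535 for loss to follow-up. A one-sided McNemar test at 0.05 with 80% power and odds ratio 1.5 has p = 1.5/2.5 = 0.6 among discordant pairs. It needs (1.645 × 0.5 + 0.842 × √(0.6 × 0.4))² / (0.6 − 0.5)² ≈ 152.5 discordant pairs. The article does not state the discordant proportion, so 374 cannot be fully reproduced; it follows if that proportion is about 152.5/374 = 0.41. The inflated figure fits an implied 30% loss: 374/0.70 = 534.3, rounded up to 535. Nothing below depends on how 374 was reached; the two totals only set the clinic size.

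**Inputs for the check**
- Clinics: 7 (Intervention), taken as the allocated clusters and as equal in size (assumption).
- Total: 535 at enrolment or 374 evaluable (Sample Size Calculation).
- ICC: not given. The range 0.01 to 0.05 is assumed, with 0.10 as an outer value.
- Baseline tests: two-sided, judged at 5% (assumed level for these tests).

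**Formulas.** Mean clinic size m = N/7. Design effect DE = 1 + (m − 1) × ICC. Actual rejection rate of a test that ignores clustering, with no systematic difference between arms: 2 × [1 − Φ(1.96/√DE)].

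**One case in full.** N = 535 and ICC = 0.05: m = 535/7 = 76.4; DE = 1 + 75.4 × 0.05 = 4.77; 1.96/√4.77 = 0.897; rejection rate 0.370.

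| ICC (assumed) | DE, N = 535 | Rejection rate, N = 535 | DE, N = 374 | Rejection rate, N = 374 |
|---|---|---|---|---|
| 0.01 | 1.75 | 0.139 | 1.52 | 0.112 |
| 0.02 | 2.51 | 0.216 | 2.05 | 0.171 |
| 0.05 | 4.77 | 0.370 | 3.62 | 0.303 |
| 0.10 | 8.54 | 0.502 | 6.24 | 0.433 |

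**Simulation check.** Seven equal clinics split 4 against 3, 4,000 runs per case. For N = 535 at ICC 0.01, 0.02 and 0.05, the t test rejected in 13.6%, 21.0% and 36.3% of runs and the Chi-square test in 13.5%, 22.8% and 36.1%. For N = 374 the figures were 11.0%, 16.6% and 31.5% (t), and 12.0%, 17.4% and 30.4% (Chi-square). With ICC 0 all rates were between 4.8% and 6.2%. The formula and the simulation agree.

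**Use of baseline in the outcome analysis.** The before-after contrast uses the baseline vaccination rate as a change score. On a continuous scale, with correlation rho between baseline and follow-up, a change score has relative variance 2(1 − rho) and baseline-covariate adjustment has 1 − rho². Their ratio, adjusted to change, is (1 + rho)/2: 0.65, 0.75 and 0.85 at rho 0.3, 0.5 and 0.7. Rho is not given and the outcome is a proportion, so this shows only the direction of the argument. It does not measure a loss in this trial.

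**The case against.** The strongest reply is that these tests do no harm to the result. They do not feed the effect estimate, no covariate is chosen on the strength of a baseline p-value, and a clinic effect is planned for the outcome. That stands, and it limits the point to the reading of the baseline table.

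The size also rests on assumptions. The article gives no ICC and does not spell out that whole clinics are allocated, although cluster randomization with a clinic effect implies it. It speaks of participants, and those recruited are parents; if parents are the unit tested, clinic sizes would differ from those used here. All this affects how far the rejection rate exceeds 5%. With whole clinics allocated and an ICC above zero, it does exceed 5%.

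A reader might go further and infer that baseline data are collected and then left out of the analysis, at a cost in precision. The documents do not support that. The baseline vaccination rate enters through the before-after change. The covariates of the hierarchical model are not listed, but an article commonly leaves such a list to the full protocol or analysis plan, so silence is not evidence of omission. Nor would a gain in precision be certain: adding covariates to a logistic model for a binary outcome does not generally shrink the standard error of the log odds ratio.

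**Conclusion.** The baseline tests as stated do not fit a cluster randomized trial recruiting at 7 clinics. If whole clinics are allocated, clinics are of similar size and the ICC is between 0.01 and 0.05, a nominal 5% test would be significant about 14% to 37% of the time at N = 535 and 11% to 30% at N = 374, with no systematic difference between the arms. At ICC 0.10 the figures are about 50% and 43%.

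This is a minor point, because only the interpretation of the baseline table is affected. Entering baseline variables as covariates is a worthwhile improvement to the outcome model, but its absence is not an error shown by the article.

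**What to change.** Remove the baseline t and Chi-square tests. Present baseline characteristics descriptively by arm and by clinic, without p-values, so that readers can judge the size of any difference and whether one or two clinics drive it.

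As an optional improvement, name in advance the baseline variables that enter the planned hierarchical model at the individual level, and use that model rather than rely on the unadjusted before-after change. Candidates are baseline vaccination status and electronic health literacy, plus child age or next due dose if recorded. Age is worth considering because Table 1 schedules nothing between 18 months and 6 years, while eligibility covers 0 to 5 years, so age bears on whether a dose falls due during the study.

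The cost is a change of wording. The listed baseline data are already to be collected, and individual-level covariates use no clinic-level degrees of freedom.

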### Sample Size Calculation

The sample size was calculated using G*Power 3.1.9.2 for testing the effect of the intervention by McNemar test. For 1-tailed hypothesis, at a power of 80% and level of significance of 0.05, a sample of 374 children is needed to detect a clinically important change in the proportion of children who will come back for their follow-up doses after introducing the intervention (ie, odds ratio of 1.5) [25]. After adjusting to potential proportion of lost to follow-up, the estimated sample size becomes 535. The analysis will be performed using Stata Statistical Software: Release 14 (College Station, TX: StataCorp LP.).

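### If clinics are the randomized units there are at most 7 clusters, and the planned hierarchical model needs a stated small-sample method to hold its 5% level

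*Protocol article*

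**What the plan says.** Study Design gives the label: "This will be a cluster randomized controlled trial to evaluate the effectiveness of using an app to record the vaccination schedule". The same section says how sites enter: "The vaccination sites will be enrolled on the basis of convenience, because of the security situation in the refugee camp". The Intervention section gives their number, with recruitment by "trained volunteers at the 7 local clinics, providing vaccinations, around the Zaatari camp". Seven is therefore a ceiling on the number of clinics.

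Statistical Analysis names the clinic as the level of clustering: "Hierarchical level modeling will be conducted to consider any cluster effect of the clinics". The software is Stata, release 14. The other between-arm steps in that section (baseline t and Chi-square tests, change in rates, Cohen d, survival analysis) make no mention of clustering.

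The article gives no ICC, no split of clinics between arms, no control return rate, and no estimator, reference distribution or degrees of freedom for the model. A significance level and a sidedness appear only under Sample Size Calculation: "For 1-tailed hypothesis, at a power of 80% and level of significance of 0.05, a sample of 374 children is needed", for a McNemar test.

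**The concern.** When whole clinics are allocated, the arm effect is a difference between two small groups of clinics. With 7 clinics in two arms, the variance that governs it is estimated from 7 - 2 = 5 degrees of freedom, however many children each clinic recruits. A z-test treats that variance as known. ML also divides by the number of clinics rather than by clinics minus 2, and so estimates the variance too low.

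The hierarchical model is the only step that the article describes for clustering. Run in its ordinary form, it would give intervals that are too narrow, and ordinary differences between clinics could be reported as an effect of the app.

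**Working it through.** **Inputs from the article.** At most 7 clinics; 374 children, or 535 after loss to follow-up; level 0.05; one-tailed for the sample size; binary outcome (on-time return).

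**Assumptions, because the article gives no figure.** A 4 v 3 split, equal clinic sizes, 50% return under no effect, and ICC from 0 to 0.05.

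**The plan's own figure.** For McNemar with odds ratio 1.5, the share of discordant pairs favouring the app is 1.5/2.5 = 0.6. The pairs needed are (1.645 × 0.5 + 0.8416 × √(0.6 × 0.4))² / 0.1² = 152.5. So 374 children implies a discordant proportion of 152.5/374 = 0.41, which the article does not state. The figure is attainable but cannot be verified. 535 equals 374/0.70, which implies 30% loss. Neither figure contains a term for clustering.

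**Limiting error with a normal reference.** When variation between clinics dominates, with k clinics:
- REML, two-sided: P(|t| > 1.96) on k - 2 df
- ML, two-sided: P(|t| > 1.96 × √((k - 2)/k)) on k - 2 df
- One-sided: 1.645 in place of 1.96, one tail

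| Clinics | Two-sided REML | Two-sided ML | One-sided REML | One-sided ML |
|---|---|---|---|---|
| 7 | 10.7% | 15.9% | 8.0% | 11.2% |
| 6 | 12.2% | 18.5% | 8.8% | 12.5% |
| 5 | 14.5% | 22.6% | 9.9% | 14.6% |
| 4 | 18.9% | 30.0% | 12.1% | 18.2% |

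**Simulated error, no true effect.** 7 clinics, 374/7 ≈ 53 children each, linear mixed model on beta-binomial data, 40,000 trials per row:

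| ICC | ML two-sided | REML two-sided | ML one-sided | REML one-sided | Clinic-level t, 5 df |
|---|---|---|---|---|---|
| 0 | 4.4% | 3.8% | 4.4% | 3.9% | 5.1% |
| 0.005 | 7.0% | 5.5% | 6.2% | 5.2% | 5.0% |
| 0.01 | 8.8% | 6.8% | 7.5% | 6.0% | 5.2% |
| 0.02 | 11.6% | 8.5% | 9.0% | 6.9% | 5.1% |
| 0.05 | 14.6% | 10.2% | 10.3% | 7.7% | 5.2% |

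A random-intercept logistic model with a Wald z-test behaves similarly: 10.2% at ICC 0.02 and 16.2% at ICC 0.05 with 374 children (about 1,000 trials each, Monte Carlo standard error about 1 percentage point). At 535 children, control rates of 25% or 80% change little.

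**Width.** The two-sided critical value on 5 df is 2.571, and 2.571/1.960 = 1.31.

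**Power of the 5-df test.** Take 50% v 60% return (odds ratio (0.6/0.4)/(0.5/0.5) = 1.5) and m = 374/7 = 53.4 children per clinic. The standard error is √[(0.25/4 + 0.24/3)/m × (1 + (m - 1) × ICC)].
- ICC 0.02: design effect 2.05, standard error 0.074, noncentrality 0.10/0.074 = 1.35. Power is 20% two-sided, 32% one-sided.
- ICC 0.05: design effect 3.62, standard error 0.098, noncentrality 1.02. Power is 13% two-sided, 22% one-sided.

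**The case against.** The strongest reply is that the article does not choose a normal reference. It names a class of model, and that class is compatible with small-sample degrees of freedom. A condensed article may leave the estimator and the reference distribution to a fuller plan that is not shown. This stands in part. A reader might infer that the trial will run at two to three times its nominal error, but the documents do not support that as a statement about the plan. It describes one unstated, though ordinary, way of running the model. What remains is that the article commits to this model on at most 7 clusters, and nothing shown rules out the reading that fails.

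Second, the randomized unit is never stated. Study Design describes the arms by participant after consent, and under Assessments each child's card is marked by arm, which would be less needed if every clinic held one arm. If families were allocated within clinics, variation between clinics would largely cancel from the arm contrast and this inflation would not arise. Clinic allocation is the natural reading, since no other cluster is named, but it is an inference.

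Third, the size depends on quantities that the article does not give. At ICC 0.005 the inflation is modest, at ICC 0 there is none, and REML or a one-sided test roughly halves the excess. All of this stands, and a single multiple without ICC, estimator and sidedness would overstate the case.

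**Conclusion.** The point holds conditionally. If clinics are the randomized units, a hierarchical model read against a normal reference would not hold 5% with 7 clinics unless the ICC is close to zero. Over ICC 0.005 to 0.05, two-sided error is 1.4 to 2.9 times nominal by ML (7.0/5 to 14.6/5) and 1.1 to 2.0 times by REML (5.5/5 to 10.2/5). One-sided error, the only sidedness that the article states, is about 1.0 to 2.1 times nominal across the two estimators (5.2/5 to 10.3/5). Fewer clinics make it worse.

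These figures rest on the assumed ICC range, the 4 v 3 split, equal clinic sizes and 50% return. It should not be read as established that the plan uses a z-test, that clinics are certainly the randomized units, or that fewer than 7 will take part. Convenience enrolment only makes the last of these possible.

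**What to change.** State the randomized unit. If it is the clinic, make the primary arm comparison a t-test on clinic-level proportions, covariate-adjusted if wished, with clinics minus 2 degrees of freedom. In the simulations this gives about 5% at every ICC tried.

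A linear mixed model on the binary outcome with Satterthwaite or Kenward-Roger degrees of freedom is an alternative. Those corrections do not carry over to a logistic mixed model, so the scale must be named.

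A permutation test over the clinic allocation can serve only as a check. Seven clinics split 4/3 give 35 allocations and a smallest p of 1/35 = 0.029. Six split 3/3 give 20 allocations and a smallest two-sided p of 2/20 = 0.10.

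The text costs one or two sentences and no new data. The statistical cost is real: intervals about 31% wider than with 1.96, and power far below the planned figure (13% to 20% two-sided or 22% to 32% one-sided under the assumptions above). The 80% belongs to the McNemar calculation and should not be quoted for the comparison between arms.

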### Ethical Considerations

This study has been reviewed and approved by the Institutional Review Board of the Jordan University of Science and Technology (Reference# 14/112/2017, date January 14, 2018). In addition, the project proposal has been endorsed by the Minister of Health in Jordan, UNICEF-Jordan. Owing to the vulnerability of the refugees and the context of the camp, all participants will be invited to participate on a volunteer basis. Survey data will be collected at baseline followed by a survey at the end of the study. Participants will be given ID numbers, and these numbers will be stored in the app of each participant. No personal information will be stored. The research assistants will review the schedule of the app and match it against the standardized tool for the vaccination schedule of Jordan-Ministry of Health. Study participants will have their full right to cancel their participation in the study, including closing their study file. The data will be entered and stored in a secured database, using EpiData [28], and only team members will have access to it. Any reports or publications will be anonymized, and no identifying information will be included.

### Benefits for the Refugees

Few studies exist in the published literature, which focus on vaccination, health information, and the needs of refugee population [29,30]. This study will determine the immunization coverage gap and attempt to reduce it among refugee population in 3 different settings and evaluate a newly designed and piloted app to replace traditional paper-based immunization and health care records, which are not an option among a traveling/mobile population [31]. This will enable refugees to keep a record of vaccinations and prevent VPDs.

### Communications and Dissemination Strategy

Before the launching of the study in March 2019, we held a briefing meeting with the representatives of the clinics, social workers, and health care workers of the camp. Thereafter, bimonthly progress meetings will be conducted with the same group of representatives. This will help the development of the policy document related to immunization in the 3 countries. The results will be published in open-access peer-reviewed international scientific journals to enable wider access inside and outside these countries, especially among low- and middle-income contexts. This will benefit other countries in improving their vaccination programs, using smartphones.

## Results

The study enrolment is still ongoing. We expect to complete the study by October 2019 followed by data analysis and submission of the final report by the end of 2019.

## Discussion

This paper describes the study protocol for a randomized controlled trial of a smartphone app on child vaccination at one of the largest Syrian refugee camps in the world. Owing to the current gap in children vaccination coverage in Jordan, this study will provide an important preliminary insight on using a smartphone app to improve child immunization in a refugee camp, and this study will be unique in certain ways. First, according to our knowledge, this is the first cluster randomized controlled trial of a smartphone app–based intervention to support the national vaccination program. This includes the effects on the immunization coverage, follow-up visits, and the experience of both of health care staff and parents in using the app. The outcome of this study will be of high importance for the different collaborators, including UNICEF, UNHCR, and the Jordan-Ministry of Health.

